### Participant timeline {13}

The duration of the trial is 12 weeks and the supervised intervention duration is 8 weeks. The participants will be assessed at baseline and 4, 8 and 12 weeks’ follow-up.

### Sample size {14}

Sample size was calculated using the WinPepi version 11.65 statistical software. Results from a study by Jeitler et al. [11] with patients with chronic neck pain were used to calculate the sample size. In sample size estimation, we used the standard deviation values of the intervention group (17.2) and the control groups (21.5) after 8 weeks of treatment as stated in the study done by Jeitler et al. [11]. According to this study, the baseline pain value (45.5 SD 23.3) in the intervention group reduced to (21.6 SD 17.2) after 8 weeks of treatment and the baseline pain value (43.8 SD 22) in the control group reduced to (37.7 SD 21.5) after 8 weeks of treatment. Therefore, we considered 17.8 as the minimally important clinical difference. Using these values and a power of 80%, ratio of 1:1 and a significance level of 5%, the sample size was calculated. According to the calculation, the total sample size was 76 and number of patients for each arm of the trial was 19. According to an RCT conducted by Rantonen et al. [25] involving three intervention groups and a control group, the dropout rate was 26%. If we use this 26% dropout rate, and to maintain a total sample of at least 76, we need to have at least 26 patients per each arm of the trial. No adjustments will be made for multiple testing.

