### Objectives {7}

[SPIRIT guidance: specific objectives or hypotheses.]To compare the effectiveness of three different meditation techniques:AnapanaBody scanMetta

with a usual care control group and with each other, at 4, 8 and 12 weeks’ follow-up on patients’ perceived neck and shoulder region pain, range of movement at the neck and shoulder and changes in physical and social disability relating to activities of daily living, occupation and social activities with family and friends.Explore how patients in each intervention group feel about the effectiveness of meditation for their chronic neck and shoulder region pain.

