## Statistical methods

### Statistical methods for primary and secondary outcomes {20a}

Descriptive statistics (means, SDs, percentages, *T*-tests, chi-square tests) will be used to describe patient characteristics at baseline, differences between groups at baseline, and for all outcomes at each follow-up time point (4-, 8- and 12-week follow-up). The significance level that will be used is 5% (corresponding 95% confidence intervals will be presented) [26] and the SPSS statistical soft wear version 21 will be used in data analysis. If data is normally distributed, a two-way ANOVA will be used to explore any changes in the primary outcome between patients in the three intervention arms (Anapana, Body Scan and Metta) and the usual care control group between baseline and the 8-week follow-up. Similarly, any changes in secondary outcomes between the four arms (three intervention arms and the control arm) will be explored at 4- and 12-week follow-ups. If the data is not normally distributed, a nonparametric equivalent, such as Kruskal-Wallis, will be used.

Treatment effects (between group differences) will be presented with corresponding confidence intervals.

Multivariate linear regression will be used to explore any effect of the independent variables of age, gender, level of income, level of education, changes in the amount of medication used and the weekly, mean meditation duration on the primary outcome at 8-week follow-up and in the secondary outcomes at 4- and 12-week follow-up. However, because they are not assessing differences between treatment arms, multivariate regression analyses will only be exploratory.

All focus groups will be audio-recorded and transcribed verbatim and translated to English [27]. For the qualitative data analysis, the literature recommends a scientific model be used [27]. To do this, the Richie and Spencer model will be used as it provides a sound analytical model [27]. ATLAS.ti will be used to manage the analysis due to its usefulness for coding.

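### The 19 per arm is a two-group calculation, while the named primary test compares four arms; the plan does not say which comparison the 80% power covers, and for the four-arm test it is about 62% to 92% depending on an unstated pattern of means

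*Protocol article*

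**What the plan says.** The sample size section (item 14) draws on a cited trial in chronic neck pain. It takes the SDs at 8 weeks as 17.2 (meditation) and 21.5 (control), and states that "we considered 17.8 as the minimally important clinical difference". It continues: "Using these values and a power of 80%, ratio of 1:1 and a significance level of 5%, the sample size was calculated". The result is that "the total sample size was 76 and number of patients for each arm of the trial was 19". Enrolment is raised to 26 per arm for 26% dropout, and the section declares that multiple testing will not be adjusted for.

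The statistical methods section (item 20a) says, for the primary outcome, that "a two-way ANOVA will be used to explore any changes in the primary outcome between patients in the three intervention arms" and usual care, with Kruskal-Wallis if the data are not normal. The abstract names the same tests. Item 20a adds that between-group differences will be shown with confidence intervals, but it does not call any one of them the primary comparison.

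The objectives (item 7) are to compare the three techniques "with a usual care control group and with each other, at 4, 8 and 12 weeks" of follow-up.

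**The concern.** The sample size was worked out for one test and the primary outcome is to be judged by another. A comparison of two means needs one difference and an SD. A four-arm test of equal means has 3 degrees of freedom for arm, and its power depends on where all four means lie. The sample size section gives no such pattern, so its 80% cannot be read as the power of the four-arm test in general.

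There are two practical consequences. First, if one technique achieves the full planned benefit and the others achieve part of it, the four-arm test can miss the difference more often than the printed figure suggests. Second, a significant four-arm result does not show which technique differs from usual care, which is the question the trial asks.

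The single power figure is also unqualified. Its inputs come from a meditation programme compared with physical exercise (background section, item 6a), so they give no basis for power between one technique and another, although those comparisons are also an objective.

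**Working it through.** **Inputs** (sample size section): difference 17.8 = (45.5 − 21.6) − (43.8 − 37.7); SDs 17.2 and 21.5; ratio 1:1; significance level 5%; power 80%. Sidedness is not stated. Two-sided is assumed because it returns the printed 19; one-sided would give 15.

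**1. The plan's own figure.**
n per arm = (1.960 + 0.842)² × (17.2² + 21.5²) / 17.8² = 7.849 × 758.09 / 316.84 = 18.78, rounded up to 19.
4 × 19 = 76. With 26% dropout, 19 / 0.74 = 25.7, so 26.
All the printed numbers reproduce, and nothing in them reflects four arms except the multiplication by four.

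**2. Power of the four-arm test with 19 per arm.** Assumptions, because the document does not settle them: one-way F test, independent patients, common SD = √[(17.2² + 21.5²)/2] = 19.47 (variance 379.05), lowest and highest arm 17.8 apart.
Degrees of freedom are 3 and 4 × 18 = 72. The noncentrality is λ = 19 × Σ(μᵢ − μ̄)² / 379.05.

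| Pattern of the four means | Σ(μᵢ − μ̄)² | λ | Power |
|---|---|---|---|
| 0, 8.9, 8.9, 17.8 (others at the midpoint) | 158.42 | 7.94 | 62.4% |
| 0, 5.93, 11.87, 17.8 (evenly graded) | 176.02 | 8.82 | 67.5% |
| 0, 17.8, 17.8, 17.8, or 0, 0, 0, 17.8 | 237.63 | 11.91 | 81.5% |
| 0, 0, 17.8, 17.8 (two and two) | 316.84 | 15.88 | 91.8% |

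The first row is the minimum and the last the maximum for a fixed gap of 17.8 between the extremes. Reaching 80% in the first row would take 28 analysable patients per arm.

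**3. Sensitivity to the SD.** The trial has one usual-care arm and three technique arms, so the protocol's own SDs would be 21.5 once and 17.2 three times. Simulated F-test power with usual care as an extreme arm is then about 67% at the midpoint, 72% evenly graded, and 83% if all three techniques beat usual care by 17.8. Kruskal-Wallis in the same setting gives about 62% at the midpoint and 69% evenly graded.

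**4. Power of one contrast, a technique against usual care.**
Noncentrality = 17.8 / (19.47 × √(2/19)) = 17.8 / 6.317 = 2.82.
With the four-arm error term (72 df), unadjusted two-sided 5%: 79.4%. From the two arms alone (36 df): 78.3%. This is the comparison that the printed calculation describes.

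**The case against.** A reader might infer that power drops to 62% whenever the other two arms lie between the extremes. The documents do not support that. The 62% needs both other arms exactly at the midpoint and a common SD of 19.47. Other intermediate positions give more, and the protocol's own unequal SDs give about 67% even at the midpoint.

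The most direct reading of the sample size section is one meditation effect applied to each meditation arm. Under that reading the four-arm test has about 81% to 83%, and nothing is lost. The document neither states that pattern nor excludes it.

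The powered comparison is also not absent. Item 20a promises between-group differences with confidence intervals, item 14 declares no multiplicity adjustment, and nothing makes the intervals conditional on a significant four-arm result. Unadjusted 95% intervals amount to unadjusted 5% tests, and these keep about 79%.

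The modelled test is itself an assumption. The second factor of the two-way ANOVA is not defined, and allocation by clinic day sits uneasily with independent patients.

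All of this stands, and it limits the size of the point. What remains is a mismatch between two printed sections. Details of contrasts can be left to an analysis plan, but here the article names the test for the primary outcome, prints a power figure derived for another test, and does not say which comparison that figure covers.

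**Conclusion.** The point holds as a mismatch between the calculation and the named test; the printed arithmetic is correct. The stated 80% describes a two-group comparison. For the four-arm test the same 19 per arm gives 62% to 92% at a common SD of 19.47, according to a pattern of means that the protocol does not state. One technique-versus-usual-care contrast has about 79%.

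These figures rest on a one-way F test, independent patients, a two-sided 5% level and 19 analysable patients per arm. If all 26 enrolled per arm were analysed, the least favourable case would rise to 78%.

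It would go too far to conclude that the trial has 62% power or that its enrolment is too small. The sample size suits the unadjusted contrasts with usual care, and the plan needs to say that these are what it powers.

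**What to change.** In the statistical methods section (item 20a), name as the primary analysis the three contrasts of each technique with usual care in change in pain at week 8, estimated from one four-arm model with a pooled error term. Report the four-arm test as supportive. Align the abstract with this.

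In the sample size section (item 14), state that the roughly 80% power (79% by the t test) applies to one such unadjusted contrast under the stated inputs and independent patients. State also that it does not apply to the four-arm test in general or to comparisons between techniques, and that the latter are reported as estimates with confidence intervals.

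The cost is rewording in these places and slightly different software output. The power statement becomes less favourable for the four-arm test and the between-technique comparisons. Enrolment does not change.

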### Recruitment {15}

All patients who are not currently being treated for neck and shoulder pain in this clinic who meet the eligibility criteria and who attend the clinic on one of the intervention clinic days will be notified about the research study by an independent person (nurse). Patients who show their willingness to participate will be provided more information about the project and their written consent will be obtained prior to recruitment.

## Assignment of interventions: allocation

### Sequence generation {16a}

This is a four-arm parallel-group trial carried out in a single medical centre which has four clinic days. Each clinic day will be allocated to an intervention arm randomly, using the lottery method, by a person independent of the trial team. The allocation sequence will be computer generated. After a period of 6 months, the clinic days will be reallocated to intervention arms using the lottery method.

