### Study limitations

This is a four-arm parallel clinic-level randomised controlled trial. There can be issues related to clustering effects and allocation concealment. Therefore, allocation to a certain clinic day will be based on availability of sessions rather than patient characteristics, and all patients attending sessions on the relevant days will be systematically invited into the study. The similarity of study participants between intervention groups at baseline will be assessed.

In a randomised controlled trial, patients (or in this case clinic days) are randomly allocated to intervention or control arms. Therefore, patients may receive a meditation intervention that may not be the ideal technique for them personally. In this study, patients will be asked to meditate for at least 15 min/day on their own at home and record the practice duration in a logbook. Therefore, it will not be definitively possible to assess whether the meditation is actually performed or to assess the quality of meditation practised. Other limitations of the study is that analyses may be affected by imbalances between groups at baseline and the limited number of patients in each arm of the trial.

In the present study, expected loss to follow-up is high and potentially puts the study at risk of bias. To reduce dropouts in our study, the patients will be taught about the benefits of regular meditation prior to teaching them meditation. If patients experience any difficulty during their daily meditation practice, they have the facility to discuss them with the meditation instructor

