## Trial status

Initial Protocol version numbers were 01 and date 08.03.2022; 02 and date 10.08.22.

Amended Protocol version number is 03 and date 21.09.2022.

At the time this protocol paper was submitted, recruitment had not begun due to the COVID-19 pandemic situation in Sri Lanka. We anticipate that it will take 1 year to recruit and an additional 3 months to complete the monitoring. By the time we received reviewer comments on the manuscript, recruitment had started (recruitment start date: 18/04/2022).

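### Clinic days are re-randomised at 6 months, but recruitment is not spread across the switch and the primary model has no term for half, so uneven filling would carry any shift between halves into the arm comparison

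*Protocol article*

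**What the plan says.** Sequence generation {16a} ties arms to days: "Each clinic day will be allocated to an intervention arm randomly, using the lottery method". It adds one later change: "After a period of 6 months, the clinic days will be reallocated to intervention arms using the lottery method". Sample size {14} sets a single recruitment figure: "we need to have at least 26 patients per each arm of the trial". Trial status gives the time frame: "We anticipate that it will take 1 year to recruit and an additional 3 months to complete the monitoring". The redraw therefore falls about midway through recruitment.

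Study limitations gives the invitation rule: "all patients attending sessions on the relevant days will be systematically invited into the study". No section links recruitment to the switch. There is no number per arm per half, and no rule for an arm that reaches 26 before month 6. Statistical methods {20a} describes a two-way ANOVA across the four arms for the primary outcome and names neither half nor weekday as a factor.

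**The concern.** Within either half each arm sits on one clinic day, so arm and weekday coincide. The redraw is the only stated feature that can loosen this tie, and it moves an arm to another day only if that arm recruits on both sides of the switch.

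The redraw also makes the half the period within which days are randomised to arms. If two arms draw different proportions of their patients from the two halves, a change over time in case mix or usual care no longer cancels in their comparison, and an analysis without a term for half attributes that change to treatment.

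**Working it through.** **Inputs from Sample size {14}.** The calculation uses "standard deviation values of the intervention group (17.2) and the control groups (21.5) after 8 weeks of treatment". For the difference to detect, it states "we considered 17.8 as the minimally important clinical difference". Power is 80%, the ratio 1:1 and the significance level 5%, taken here as two-sided because the sides are not stated. Dropout is 26%. I read these values as being on a 0–100 scale, so 5 or 10 points correspond to 0.5 or 1.0 on the trial's 0–10 scale.

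**The plan's own figures reproduce.**
- n = (17.2² + 21.5²)(1.960 + 0.842)² / 17.8² = 18.78, rounded up to 19 per arm.
- 19 / (1 − 0.26) = 25.7, rounded up to 26 per arm.

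**Expected pace.** 26 patients over 52 weeks is 0.5 per week per arm, or 13 per half. If each of the 26 is equally likely to fall in either half, a split of 20/6 or worse in either direction has probability 0.9% for one arm and about 3.7% for at least one of four. The pace is not fixed, however. With Poisson arrivals at an assumed 0.75 per week, the chance of 20 or more in the first half is 48%. At an assumed 1 per week it is 90%, and the chance of reaching 26 in that half is 53%.

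**Bias without a term for half.**
- Bias b = (difference between the two arms in the share recruited in one half) × (shift in mean outcome between halves).
- SE = √((17.2² + 21.5²)/19) = 6.32.
- False-positive rate = Φ(−1.96 + b/SE) + Φ(−1.96 − b/SE).

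The shifts of 5 and 10 points are assumptions, and dropout is taken not to change the shares.

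| Split of one arm (other arm 13/13) | Share difference | Shift | Bias | % of 17.8 | False-positive rate |
|---|---|---|---|---|---|
| 20/6 | 20/26 − 0.5 = 0.269 | 5 | 1.3 | 8% | 5.5% |
| 20/6 | 0.269 | 10 | 2.7 | 15% | 7.1% |
| 26/0 | 0.5 | 5 | 2.5 | 14% | 6.8% |
| 26/0 | 0.5 | 10 | 5.0 | 28% | 12.4% |

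**Precision cost of adding half.** In a model with arm and half, the variance of a contrast between the uneven arm and an even one, in units of σ², is 2/26 + d²/S. Here d is the share difference and S is the sum over the four arms of 26·w(1 − w), with w the share in the first half.
- All arms 13/13: 2/26 = 0.0769.
- One arm 20/6: S = 19.5 + 4.62 = 24.12; variance 0.0769 + 0.0725/24.12 = 0.0799, or 1.04 times.
- One arm 26/0: S = 19.5; variance 0.0769 + 0.25/19.5 = 0.0897, or 1.17 times.

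**Weekday.** I enumerated all 24 possible redraws and checked which of the six arm contrasts can be estimated with arm, weekday and half in the model. With every arm recruiting in both halves, all six are estimable in only 6 of 24 redraws. If one arm recruits only in the first half, no redraw makes all six estimable (at most three), and the six redraws that did so before now allow none.

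**The case against.** The strongest reply is that the plan already implies balance: a year of recruitment gives about 13 per half, and at that pace a split as uneven as 20/6 is rare. That stands, and it makes this a risk and not a forecast. Nor does the article document differences in patient volume between days.

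A second reply is that 26 is a minimum. No section closes an arm at 26, so 26/0 needs a closing rule that the article does not contain. That also stands; 26/0 marks the extreme.

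A third is that quotas and covariates belong in the full protocol or the analysis plan, neither of which is shown. Either could supply them. But the article itself states the redraw, the target, the invitation rule and the form of the primary analysis, and leaves them unconnected. Its remedies in Study limitations (placement by session availability, systematic invitation, a baseline comparison) do not address when each arm fills.

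A reader might infer that an early-filling arm cannot be compared with the others at all. The documents do not support that. With arm and half in the model every contrast remains estimable. Contrasts are lost only if weekday is added as well, and which ones depends on the draw. A reader might also infer that equal shares would free arm from weekday. They would not, because the lottery as described is unrestricted.

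**Conclusion.** The point holds as a moderate weakness in the design. A redraw at mid-recruitment, one overall target per arm and a primary model with no term for half leave the arm comparison open to a shift between halves if arms fill unevenly. At 20/6 the effect is modest: 1.3 or 2.7 points of bias and a 5.5% or 7.1% false-positive rate. At 26/0 it reaches 2.5 or 5.0 points and 6.8% or 12.4%. These sizes rest on an assumed shift of 5 or 10 points for which the article gives no figure. They also require arms to fill at different times; if all four filled in the same half, calendar time would cancel and only the tie to weekday would remain.

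An arm recruited wholly in one half is seen on a single weekday, so the redraw does nothing to separate that arm from its day. For an arm recruited mostly in one half, the separation is weakened and not lost.

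**What to change.** In Statistical methods {20a}, include half (first or second 6 months, the period within which days were randomised) as a fixed term in the primary model. The cost is one parameter and the small loss of precision shown above. The Kruskal-Wallis fallback has no place for such a term, so a version stratified by half would have to be named.

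In Sample size {14} and Sequence generation {16a}, state that every arm is to recruit a substantial share after the switch, with about 13 of 26 as a target, and report enrolment by arm, clinic day and half. The total stays at 4 × 26 = 104.

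A hard cap of 13 is not advised. It would close a whole clinic day against the systematic invitation of all attenders, and it fits badly with teaching sessions of five. It would also have come late: recruitment began on 18/04/2022 and version 03 is dated 21.09.2022, about a month before the first half ended. A second-half target could still be applied then, including to an arm already at 26, since 26 is a minimum.

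This removes additive calendar-time bias between halves. Separating arm from weekday is a further matter that depends on how the second draw is made and on modelling weekday.

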### Concealment mechanism {16b}

Allocation concealment will be implemented using sealed opaque envelopes. The usual care givers (doctor and the physiotherapist) and the physiotherapist who will be assessing the outcomes will not be aware of the randomisation allocation.

### Implementation {16c}

The allocation sequence will be generated by an independent statistician. Participants will be assigned to intervention groups and the control group by a clinic nursing assistant according to the instructions by the independent statistician. Study implementation will be completed by the researchers.

## Assignment of interventions: blinding

### Who will be blinded {17a}

Participants will be informed about the four trial arms at the time of agreeing to give informed consent. They are also informed that allocation of the four trial arms will be decided on a random basis. Participants in one arm will not know about the details of interventions that are given to participants in other arms.

